Whilst there continues to be debate over the design and its limitations (e.g. [59]), some of which are valid, evaluations of public health interventions often have to be pragmatic and take into account the stakeholders and context of the intervention involved (in this instance the contact centres). We argue that we need a pragmatic option for a number of reasons. First, it could potentially cause delays in the evaluation process if we waited until all contact centres were at the same stage of readiness for implementation. A structural/location/organisation change in one contact centre could delay the process. Second, it would be more costly and resource intensive to implement the intervention and collect baselines data in all the contact centres at a single time point. We have requested two researchers, but due to the spread of locations in Scotland and North East England, this would make implementation and data collection difficult and increase the potential for failure. Third, contact centres are already wanting to implement the intervention when they hear about it. It is unlikely to cause any harm. It has been implemented in one contact centre for over a year and only positive benefits have been reported. Journals such as The Lancet Global Health and Trials are publishing the results of such designs [e.g. 60, 61].

Setting

Ten contact centres with more than 100 employees in Scotland and/or the North East of England. These two areas have the highest rates of contact centres in the UK, employing up to 6% of the workforce in these regions [62]. We will consider other areas of England if there is interest and to ensure we have 10 contact centres taking part.

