## Randomisation

Randomisation will occur in month three. The unit of randomisation is contact centres. A computer-generated block randomisation algorithm will be used to randomly allocate each contact centre to start the intervention at one of five time points, three months apart. Randomisation in this way allows us to introduce the intervention to each site in an unbiased way unrelated to time or the particular circumstances of each site. It also helps ensure there is approximate balance on average across all the intervention start times in terms of participant or contact centre characteristics.

Steps to minimise bias

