### Duration of the intervention:

Duration of the intervention is defined as the period in which the centres take to develop their preferred activities for each theory of change, prepare an action plan for sustained engagement and test out some of the activities. This process is expected to take around three months, but may be dependent on the contact centre.

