### Data collection timepoints

In order to minimise cost and participant burden for this trial, and since the main purpose of the trial is to test study processes and procedures, data will only be collected at a maximum of three occasions per site: at the end of the control period, and at 3 and 6 months after the end of the intervention in each site. Sites 1 and 6 will not have a control period, and sites 5 and 10 will not have a post-intervention period, in order to minimise the duration of the study for which there is no concurrent vertical comparison between control and post-intervention periods. To increase the response rate, participants will be paid a small amount (£5 end of control period and £10 for 3 months data) for taking part in data collection.

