### Statistical analysis

The statistician will be blind to the allocation of the contact centres. The analysis and presentation of results will adhere to CONSORT guidance [73], and a statistical analysis plan. The analyses will be exploratory to investigate if it’s feasible to fit such a model in a future trial. We will not interpret the results as confirmatory and it is not the primary analysis of the trial.

Sedentary time in the workplace and all continuous secondary outcomes will be analysed using linear mixed effects regression analysis; including site and participant as random effects; and adjusting for calendar time since start of study, season (spring, summer, autumn, winter), and an indicator variable for whether the intervention has been implemented or not as fixed effects. Using observed data from all participants, 95% CI of the intervention effect sizes will provide a guide to indicate the likely effect sizes that we will observe in a future study. Sensitivity analyses will be incorporated to explore the effects of missing data and staff turnover to aid the design of a definitive trial. The assumptions underlying the sample size calculation performed by a similar study [49] will be tested and compared to the estimates we calculate using real data from the feasibility trial (e.g. standard deviation, within-site correlation, intra-cluster correlation coefficient) to inform the power calculation for a future trial. The heterogeneity of quantitative outcomes across sites (e.g. estimated via intra-cluster correlation coefficients) and variability in intervention delivery and processes across sites is of particular interest. Information gathered from this feasibility study will help determine the feasibility of conducting a future multi-site study with a larger number of contact centres.

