## Progression criteria

We will proceed to a future larger study if all of the following are satisfied:

1. 95% confidence intervals for the primary outcome includes a clinically relevant reduction in sedentary time of 45 minutes per day or greater in favour of the intervention. This would reflect substantial progression towards accumulating recommended quantity of 2h/day standing/light activity during working hours [54] for employees in predominantly desk-based occupations.
2. Intervention successfully delivered in at least five of the sites within the study period, if at least one person in each site was able to use/experience at least one activity.
3. At least 10% of employees at a site were able to use/experience at least one of the intervention activities in the sites at which the intervention was successfully delivered.
4. Out of all the participants using/experiencing at least one of the intervention activities, primary and secondary outcome data was collected in at least 75% of participants overall.
5. Contamination between sites is low or else it is envisaged that contamination can be addressed in the study design of a future study.
6. It is envisaged that any practical difficulties in delivering the intervention across multiple sites or in measuring effectiveness can be overcome when conducting a future large-scale study.

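### The intervention indicator and the follow-up dates are not tied to the randomised start step, so late, slow or non-implementing centres can turn the estimate into a partly as-treated contrast

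*Protocol*

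**What the plan says.** The Randomisation section allocates only a start step: it will "randomly allocate each contact centre to start the intervention at one of five time points, three months apart". The Statistical analysis section then fits a linear mixed model with random effects for site and participant and fixed effects for calendar time, season and "an indicator variable for whether the intervention has been implemented or not as fixed effects".

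Outcome data are collected (Data collection timepoints) "at the end of the control period, and at 3 and 6 months after the end of the intervention in each site". The end of the intervention is set by each centre. Of the development and testing period, the Duration of the intervention section says: "This process is expected to take around three months, but may be dependent on the contact centre".

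The protocol expects that centres may depart from the schedule. Design and methods warns: "A structural/location/organisation change in one contact centre could delay the process". Progression criterion 2 requires only this: "Intervention successfully delivered in at least five of the sites within the study period".

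No section says that the indicator follows the randomised step, how a late or non-implementing centre is coded, or when a centre that never finishes is measured. The analysis is declared exploratory and not the primary analysis. Even so, the 95% confidence interval for the primary outcome is progression criterion 1, judged against 45 minutes per day.

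**The concern.** Randomisation protects a comparison between allocated steps. It does not protect one between centres that did and did not get the intervention running. The section on contact centres and health says that productivity targets work against investment in such programmes. The same pressures could plausibly affect how much staff sit, so non-delivery may not be random with respect to the outcome.

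Taken literally, the text has three consequences:

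- A centre that starts late or never implements is coded as unexposed in periods when its allocation says exposed.
- A centre that never completes has no end of intervention, so its two follow-ups have no date. An analysis plan cannot recover measurements that were never scheduled.
- A slow centre's follow-ups move later, towards the end of the study, where no centre is still a control.

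At stake are the estimate and interval that inform progression and the effect size carried into the next trial.

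**Working it through.** **Schedule.** Starts fall at months 0, 3, 6, 9 and 12, with two sites per step. Delivery takes 3 months, control data are taken at the start, and post data at start + 6 and start + 9. The protocol adds: "Sites 1 and 6 will not have a control period, and sites 5 and 10 will not have a post-intervention period". Hence:

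- control cells: 4 steps × 2 sites = 8, at months 3, 6, 9 and 12;
- post cells: 4 steps × 2 sites × 2 = 16, at months 6 to 18;
- total: 24.

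Control cells with a concurrent post cell are those at months 6, 9 and 12, which is 6 of 8. This matches the six comparisons in Sampling and sample size, and 160/6 = 26.7, about 27 per cell, with 27 × 10 = 270. Post cells with a concurrent control number 2 + 4 + 4 = 10 of 16.

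**Effect of slow delivery.** If every centre takes 3 months longer, the counts fall to 4 of 8 control cells and 6 of 16 post cells. If only sites 1 and 6 overrun by 3 months, control cells fall to 4 of 8 and post cells stay at 10 of 16. The slow centres remain coded as exposed. What is lost is concurrency.

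**Effect of coding.** The protocol gives no SD, ICC or person correlation. Assumed values are SD 125 min, ICC 0.05 and within-person correlation 0.5 of the residual, with 27 people per cell. For cells of one site:

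- shared site variance = 125² × 0.05 = 781;
- residual variance of a cell mean = 125² × 0.95/27 = 550;
- residual covariance between cells = 0.5 × 550 = 275.

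With X holding intercept, linear time, season and the indicator, V the covariance matrix of the cell means and μ the assumed cell means, the expected coefficients are b = (XᵀV⁻¹X)⁻¹XᵀV⁻¹μ. The two-centre case uses sites 2 and 7. The four-centre case uses sites 2, 4, 7 and 9. Results for the indicator, in min/day:

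| Scenario | Centres not implementing | Coded by allocated step | Coded as implemented | Their post data absent |
|---|---|---|---|---|
| −45 where delivered, 0 elsewhere | 2 | −30.4 | −45.0 | −45.0 |
| same | 4 | −23.2 | −45.0 | −45.0 |
| No effect; +30 in those centres throughout | 2 | +3.9 | −4.2 | −0.7 |
| same | 4 | −0.1 | −9.2 | −3.7 |
| No effect; +30 only in their post cells | 2 | +9.7 | −9.2 | 0.0 |
| same | 4 | +14.5 | −14.6 | 0.0 |

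The −30.4 depends on which centres fail. Over all pairs of the eight centres due follow-up, the allocated-step figure runs from −30 to −38; over all sets of four, from −18 to −27.

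A separate simulation used SD 100, ICC 0.02 to 0.10, and two of eight centres failing in relation to their sitting level. With no true effect, as-implemented coding gave −7.9 to −9.5 and dropping the failed centres' follow-up gave −4.4 to −5.7. Coding by step gave about 0. When failure was unrelated to sitting, as-implemented coding added no bias.

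**Progression criterion 1.** It is met if the lower limit reaches −45. With two centres as implemented, the SE is 15.7, so the estimate must be at or below −45 + 1.96 × 15.7 = −14.2. Under a normal approximation with no effect:

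- unshifted: z = −14.2/15.7 = −0.91, chance about 0.18;
- shifted by −4.2 or −9.2: z = −0.64 or −0.32, chance about 0.26 or 0.37.

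With four centres (SE 15.4, threshold −14.8) the chance moves from about 0.17 to 0.36 or 0.49.

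**Next trial.** If it is sized on 45 but rollout yields 30.4, the required sample is (45/30.4)² ≈ 2.2 times that planned.

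**The case against.** The strongest reply is that the wording of the indicator is also ordinary shorthand for scheduled exposure in a stepped design. The protocol defers to CONSORT and to a statistical analysis plan that is not shown and that may settle the coding. A reader might infer that the protocol recodes failed centres as controls or excludes them; it says neither. This stands for the coding. It does not cover the follow-up dates, which the protocol itself fixes.

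A reader might also infer that slow centres become controls. They do not. Control data are taken once, at the end of the control period, so longer delivery only moves follow-up later. Only a late start or non-implementation could extend control status. Nor can both literal consequences hold for the same follow-up cell: it is either measured and coded unexposed, or not measured. If it is not measured, the spurious benefit in the first model is only 0 to 3.7 min.

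The gap between −45 and −30 might be read as bias. It is a difference between two estimands. Coding by step is not immune either. If the extra sitting appears only after a centre stalls, that coding counts it against the intervention (+9.7 and +14.5), as part of what scheduled rollout produced.

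Two further points have force. Five of ten sites is a minimum, not a forecast, and delivery is defined as one person using one activity, so outright failure may be rare. And at expected values, criterion 1 gives the same answer under either coding in every scenario: with a −45 effect the interval reaches −45 both ways (for example −23.2 − 30.4 = −53.6), and with no effect it does not (at most −14.6 − 30.2 = −44.8). The coding changes the probability of passing, as shown above, not the expected result.

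**Conclusion.** The point holds in a limited form. The protocol defines neither the exposure term nor the follow-up dates by the randomised step, although it foresees departures from the schedule. If departures are unrelated to sitting, the model targets the effect where delivered rather than that of scheduled rollout: −45 against about −30 with two non-implementing centres. If they are related, and those centres' follow-up is measured and coded unexposed, the spurious benefit is about 4 to 9 min with two centres and 9 to 15 with four. The lower figures apply to a constant 30-minute excess and the higher to one arising only after stalling. All of this rests on assumed SD, ICC, person correlation and number of failing centres. With no departures, nothing is lost.

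A reader might conclude that the randomised comparison is lost and that the protocol must not proceed unchanged. The documents do not support that. The comparison is weakened only if centres deviate, bias arises only if deviation is related to the outcome, and the analysis is declared exploratory. Because its interval still gates progression, the change is a worthwhile, cheap improvement.

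**What to change.** - In Statistical analysis, define the indicator by the randomised step: 1 from the centre's allocated start plus the planned three months, whatever was delivered.
- Keep as-implemented coding as a labelled sensitivity analysis, estimating the effect where delivered.
- In Data collection timepoints, schedule post-intervention collection relative to the allocated start (6 and 9 months after it, the dates implied by three-month delivery) for every centre due one, including centres that do not complete.
- Record actual start and completion dates so that departures can be reported.

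The sample size of 27 per cell and 270 in total is unchanged, and the allocated dates are known. The coding change is wording only; the collection change alters the fieldwork calendar. There are two downsides. The effect is diluted where delivery slips, although that is the quantity a rollout trial should be powered on. And some slow centres may be measured during delivery or soon after it.

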## Process evaluation and qualitative study: (Aim 1)

We will use the **RE-AIM** framework (Reach, Effectiveness, Adoption, Implementation, Maintenance) as a framework to guide the process evaluation. RE-AIM was developed to translate research into practice [74]. We will use both quantitative and qualitative methods to explore the elements of RE-AIM:

**Reach:** the number of people (and %) in the contact centres who a) take part in one or more activities in the various components of the intervention; and b) take part in the research.

**Effectiveness:** this is not the primary outcome but we will be measuring whether there are indicators of effectiveness using the outcome measures described earlier

**Adoption:** we will explore through focus groups and talking with key stakeholders the degree to which the intervention was adopted. We will also measure engagement in the two workshops, and use of the website and other resources.

**Implementation:** we will be in regular contact with the SUH implementation group in the contact centres to assess which activities were implemented by the contact centres and why; whether all the theories of change had a corresponding activity which was implemented.

**Maintenance:** maintenance is a key feature of the intervention, so we will speak to contact centre staff (particularly the SUH implementation group) after 9 months (in contact centres that received the intervention early on) to assess the degree to which the activities have been maintained or dropped.

### Qualitative study

We will conduct an in-depth qualitative programme of research comprising of focus group discussions with a representative sample of the contact centre workforce and individual interviews with key stakeholders (i.e., members of the SUH Implementation group. Primarily, the qualitative component of our evaluation seeks to gather views and experiences of the SUH intervention activities, and implementation processes with a view to refining the Theories of Change (see Table 1) and the overall Programme Theory for SUH (see Logic Model upload). With contact centre workers, we will look to elucidate the specific mechanisms of change describing potential casual mechanisms for how SUH activities could impact on the specified short- and medium-term outcomes such as a reduction in sedentary behavior at work. We will also seek insight into why the SUH activities may not have worked as intended and any unintended consequences of the intervention. With key stakeholder interviews we will look to explore whether the process if implementation worked as intended across the different levels of the intervention activities.

The proposed study methodology will also be used for triangulation of quantitative evidence and stakeholder perceptions across multiple organisational structures, sectors and job roles. This component of our evaluation will contribute to enhancing the acceptability, reliability and replicability of future interventions in this setting. Given that there is considerable variation across the implementation of current workplace-based health policies and initiatives, this research will look to explore the generalisability of findings and identify any alternative factors influencing sedentary behaviour and physical activity in the contact centre setting. We will also explore whether and why there are differences in aspects of study procedures (e.g. uptake, retention) between different contact centres and the reasons for these. A key outcome of this study will be to develop and refine the programme theory which would be used to help guide the evaluation of any subsequent effectiveness trial.

### Sampling

Sampling will be purposive to ensure broad representation based on amount of involvement in the activities, as well as gender, age and staff member (e.g. manager, supervisor or call handler).

### Data collection

One focus group will be conducted at each intervention site (10 groups in total; approx. n = 60 individuals) with contact centre staff that took part in the activities and the research Additionally, one individual interview will take place in each site with key stakeholders involved in implementation. These will take place after 5 months. This will give contact centres time to implement the intervention fully, and participants time to try out the activities. The topic guide (focus groups with participants) and interview schedules (stakeholders) will be based around the programme theory exploring where appropriate; views and experiences of the intervention activities (and implementation of these) and impact on short- and medium-term outcomes. Additionally, we will collect qualitative data on key components of the RE-AIM framework; adoption, implementation and maintenance.

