## Recruitment

Ten contact centres will be recruited and we aim to have them recruited by month three of the project. All staff in the contact centres who have been working in the contact centre will be invited (via email through their contact centre) to be involved in the evaluation of the intervention, with the aim of recruiting 27 individuals per contact centre per data collection period for the outcome data (270 in total), and 6-8 individuals per contact centre for the qualitative data collection (60-80 in total). Staff who are interested in participating will be sent an information sheet and consent form. It will be made clear that participation, or non-participation will not affect terms of their employment.

Retention

The average annual turnover (attrition) of contact centre staff is around 24% vs 15% for other industries.  This high rate of attrition has implications for the retention and follow up of participants. The high turnover is partly due to the number of students and people looking for short term work. Whilst this is a problem for the evaluation, it maybe more positive for the success of the intervention; it has the potential to impact on a range of people, enabling them to engage with health promoting activities that may encourage the development of lifelong habits.

One of the aims of this study is to determine the retention rates for a future study.  We have a number of strategies:

1. Staff will be incentivised (£5-10 gift voucher) to complete baseline and outcome data assessments
2. If staff leave the contact centre we will explore what methods it may be possible to use to follow them up (e.g., post, email, telephone) and evaluate the most effective
3. We will record data on length of time employed in the contact centres. This data will help us determine whether turnover is higher at the beginning of the employment period (which could impact on retention rates)

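### The focus groups are confined to staff who used the activities and joined the research, which contradicts the workforce-wide sampling the protocol states elsewhere

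*Protocol*

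**What the plan says.** Three adjacent sections of the protocol describe who is in the focus groups.

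- Qualitative study: "focus group discussions with a representative sample of the contact centre workforce". The same section wants to learn why activities may not have worked, what unintended consequences arose, and why uptake and retention differ between centres.
- Sampling: "Sampling will be purposive to ensure broad representation based on amount of involvement in the activities", and also by gender, age and staff role.
- Data collection: "One focus group will be conducted at each intervention site (10 groups in total; approx. n = 60 individuals"), held "with contact centre staff that took part in the activities and the research". The section adds one interview per site with stakeholders involved in implementation. It later refers to the groups as being with participants, and sets their timing so that participants have had a chance to try the activities.

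Two other places bear on the point. The Recruitment section says that all staff "will be invited (via email through their contact centre) to be involved in the evaluation of the intervention", with a target of "6-8 individuals per contact centre for the qualitative data collection (60-80 in total"). Criterion 3 of the Progression criteria is met when "At least 10% of employees at a site were able to use/experience" at least one activity.

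**The concern.** A sample restricted to people who took part cannot represent a workforce that includes people who did not. A spread by amount of involvement is also cut off at the bottom if zero involvement is not allowed. The restriction has two conditions, activity use and research participation, and the Sampling and sample size section treats these as different things, because it separates evaluation participants from staff who only do activities.

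The staff left out are ones the stated purposes need. People who could not or would not use any activity are well placed to say why it did not work for them. People who declined the research are well placed to say why uptake of study procedures varied, which is a research question under Aim 2. Acceptability, feasibility and utilisation form the first research question of Aim 1. The RE-AIM plan assesses adoption partly through these focus groups, and the section on unanticipated outcomes uses them to elicit unintended consequences. If a site team follows the Data collection wording, all of this rests on people who adopted at least something.

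**Working it through.** **1. The plan's own figure.** One group at each of 10 sites, at the lower end of 6 to 8 people per centre: 10 × 6 = 60, which matches the stated total of about 60. The upper end gives 10 × 8 = 80. Adding the 10 stakeholder interviews to 60 gives 70, inside the 60 to 80 in Recruitment. The numbers agree; the conflict is over who is eligible.

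**2. Eligibility, section by section.**

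| Staff group | Qualitative study | Sampling | Data collection |
|---|---|---|---|
| Used activities, in the research | eligible | eligible | eligible |
| Used activities, not in the research | eligible | eligible | not eligible |
| Used few activities, in the research | eligible | eligible | eligible |
| Used none, in the research | eligible | not clear | not eligible |
| Used none, not in the research | eligible | not clear | not eligible |

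The sections agree only for staff who meet both conditions.

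**3. Whether another qualitative source fills the gap.** The interviews are with members of the implementation group, so they do not reach non-users or research decliners as such. The RE-AIM maintenance item plans conversations with staff at nine months, but mainly with the implementation group, only in early centres, and about whether activities were kept or dropped.

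**4. How large the excluded group could be.** Inputs: the 10% threshold in progression criterion 3 and, for illustration, a centre of 100 staff (the Setting section requires more than 100). Users: 0.10 × 100 = 10. Non-users: 100 − 10 = 90, or 90%. The percentage is the same at any centre size. It is the largest exclusion compatible with passing the criterion.

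**5. What this could do to an acceptability finding.** Let f be the share of staff who use an activity, and p_U and p_N the shares of users and non-users who find the intervention acceptable. The workforce value is f·p_U + (1 − f)·p_N. Hearing only users gives p_U. The difference is (1 − f)(p_U − p_N). The protocol gives none of these quantities, so the gaps below are assumptions.

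| f | gap 0 points | gap 20 points | gap 40 points |
|---|---|---|---|
| 10% | 0 | 0.9 × 20 = 18 | 0.9 × 40 = 36 |
| 50% | 0 | 0.5 × 20 = 10 | 0.5 × 40 = 20 |

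The result runs from nothing to substantial, and its sign follows the sign of the gap. The formula also treats acceptability as a rate, which focus groups do not estimate. It shows only that the answer depends on inputs the protocol does not have.

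**The case against.** The best defence is that the Sampling section is the natural place for eligibility, that it already calls for a spread of involvement, and that the Data collection clause is loose description. Taking part in the activities is also compatible with slight involvement, so only complete non-users and research decliners are in doubt. This narrows the point but does not remove it. The Data collection section repeats the idea by calling the attendees participants, nothing says which section prevails, and the two doubtful groups are the ones needed to explain non-use and non-uptake.

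Three stronger readings are tempting and are not supported.

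- A reader might infer that non-users are never heard. All staff are invited to the evaluation, which is opt-in and does not depend on use. Table 2 includes a questionnaire on use and preference, reach is counted across the centre, a second workshop reviews which activities worked, and harms have their own recording sheet. What is missing is a clear focus group or interview route.
- A reader might infer that acceptability is biased upward. Users may well be more favourable, but the protocol gives no rates by use. Users who tried an activity and dropped it can also report failure.
- A reader might infer that the groups cannot be filled: at 10% use, 27 × 0.10 = 2.7 people would meet both conditions. That combines the minimum reach threshold, an assumed independence of use and research participation, and one data collection period's sample. It also takes the research to mean the outcome evaluation only, although Recruitment covers both parts under one invitation. With the same 27 people, use of 6/27 = 22% to 8/27 = 30% fills a group, and the Sampling and sample size section expects all employees to be likely to take part in something.

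**Conclusion.** The contradiction is real and rests on the text alone: the Data collection section imposes two participation conditions that the Qualitative study and Sampling sections do not. If followed literally, it removes the main qualitative route to staff who used nothing or declined the outcome evaluation, and so weakens the answer to Aim 1 and the explanation of differing uptake. The findings would probably describe users' views. The excluded share could reach 90% of a site that just passes the reach criterion, but the protocol expects much wider use, and no bias can be quantified or given a sign from the document. The protocol should be corrected, because the change is small and the first aim depends on it.

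**What to change.** Replace the eligibility clause in the qualitative Data collection section with: *contact centre staff sampled purposively across levels of involvement, including staff who used few or no activities, whether or not they joined the outcome evaluation*. Keep 10 groups and about 60 people. No fixed quota of non-users is proposed, because the protocol gives no basis for one.

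The cost is a change of wording and a broader invitation; non-users are somewhat harder to recruit.

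If the sponsor prefers to keep the restriction, the Qualitative study and Sampling sections should be amended to match, and the focus group findings on acceptability reported as applying to participating staff only.
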